### Statistical analysis

Primary and secondary outcome measures (proportions with 95% confidence intervals or means with standard deviations) will be calculated and presented in tables. A patient flow chart will be presented to account for inclusions per hospital and drop-out.

For the primary outcome and binary secondary outcomes, multi-level mixed effect logistic regression with random time by cluster interaction will be used to compare between the cohort that has not and the cohort that has received the intervention according to the stepped-wedge schedule. Time effects will be modelled according to appropriate methods, e.g. using spline functions. For continuous secondary outcomes, multi-level mixed effect linear regression will be used and for countable secondary outcomes, multi-level mixed effect Poisson regression models will be used. Analyses will be performed using SPSS and R.

On cluster level, per-protocol analyses will be performed (i.e. if the intervention phase starts later than expected in a certain hospital, patients will be allocated to the control group until the hospital has actually crossed over). Once the intervention phase has started, individuals within that cluster will be analyzed according to the intention-to-treat principle. Adjustments will be made for temporal trends and for clusters within hospitals [17]. An economic evaluation from a hospital perspective will be performed for postoperative anesthesia follow-up of high risk surgical patients compared to standard postoperative care. The time horizon of the economic evaluation will be 30 days and one year following surgery. For reasons of efficiency, the analysis after one year will be performed in a subset of study participants. A cost-effectiveness analysis will be performed, based on the incremental costs per postsurgical visit. Standard sensitivity analysis will be performed to test whether results are robust for changing certain parameters, e.g. cost-prices. Confidence intervals surrounding the mean differential costs will be calculated by the bootstrap method. The latter will also be used to quantify the uncertainty surrounding the incremental cost-effectiveness ratio [18, 19]. Additionally, a budget impact analysis will be performed to assess the affordability of a routine postoperative visit by an anesthesia healthcare professional by relating the increase in cost due to investment in anesthesia professionals to the cost-savings due to the expected reduction in complications and hence length of hospitalization and mortality.

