## Background

Perioperative complications occur in approximately 30–40% of non-cardiac surgical patients [1] and are the leading cause of early postoperative morbidity and mortality [2]. Moreover, the occurrence of early complications seems to be associated with long-term mortality that persists for years after surgery [3]. Several studies have demonstrated that surgical complications increase the overall cost of care [4–6]. Therefore, avoiding or even early treatment of complications is valuable in terms of cost-effectiveness [5, 7].

Although there is little variation in the occurrence of complications among hospitals, the resulting in-hospital mortality related to perioperative complications varies considerably [1]. In 1992, Silber et al. created the term failure-to-rescue to describe the percentage of deaths in relation to complications per surgical procedure [8]. Depending on the type of surgery, the failure-to-rescue rate varied widely across hospitals [9, 10]. Most likely, some organizations are able to cover the needs of patients with complications better than others [1, 8, 11, 12]. A more recent trial from the ISOS group observed a failure-to-rescue rate in the range of 1.7–3.6% in a mixed cohort of more than 44,000 patients in 27 countries [13].

Factors contributing to the development of failure-to-rescue have been studied intensely over the past 15 years; however, most of the data come from national or institutional databases and only little is known about failure-to-rescue rates in Europe [13]. It has been hypothesized that regular visits by highly educated and trained health professionals such as intensive care physicians, surgeons, or anesthesiologists can contribute to a decreased incidence of complications by earlier detection and adequate treatment.

Until now, no studies have been performed on the impact of routine postsurgical anesthesia visits on the incidence of postoperative complications. Therefore, we designed a nation-wide study in which patients at risk are routinely followed up by an anesthesia professional at postoperative days 1 and 3, aiming to detect and prevent or treat postoperative complications. Based on the available literature, we hypothesized that routine postsurgical anesthesia visits decrease the incidence of failure-to-rescue and reduce postoperative 30-day mortality by 50%.

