### Research questions

What is the incidence of postoperative complications in this study cohort?Is there an impact of regular anesthesia visits on postoperative days 1 and 3 in reducing postoperative complications, 30-day mortality, and length of stay?What is the impact of the routine anesthesia visits on the time to implementation of rescue therapy, the utilization of high-care and intensive care facilities after complications, and the length of stay in these units?What is the impact of routine anesthesia visits on the quality of recovery 30 days after surgery and on the quality of life one year after surgery?Is the implementation of routine anesthesia visits after surgery cost-effective compared to standard postoperative care?

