### Outcome measures

The primary outcome measure will be the mortality at 30 days after surgery. Secondary outcome measures will be incidence of postoperative complications (in eight domains—infectious, cardiac/transfusion, pulmonary, venous thromboembolic, renal, neurological, surgical, and other—in line with Meguid et al. [14]), time to implement rescue therapy, length of stay in hospital, length of stay in a high-care unit, quality of recovery 30 days after surgery, and postoperative quality of life up to one year following surgery.

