### Sample size calculation

The calculation is based on the primary outcome parameter 30-day mortality. In an earlier Dutch study, postoperative all-cause death was 1.85% [15]. Recently, the EUSOS study observed a mortality rate of approximately 2% [16], which is in line with previous results.

We considered a difference of 50% between monitored and non-monitored patients to be clinically relevant. In order to detect a reduction from 2% to 1% in postoperative 30-day mortality, with an alpha of 0.05 and a power of 80%, and a 1:1 ratio between control and intervention group, a total of 4638 patients have to be included in a parallel randomized controlled trial (RCT) design. To compensate for inter-institutional variation, a possible time-effect inherent to the stepped-wedge design, and drop-out, we increased this sample size with 20%. The relatively uncommon approach of applying a 20% inflation factor was discussed extensively during the grant application and ethical approval processes and was finally approved by both the Netherlands Organisation for Health Research and Development and the Medical Ethical Commitee.

Thus, we estimate a requirement of 5600 patients. With eight participating hospitals, this translates into 700 patients per hospital. Figure 1 illustrates how these patients will be divided across hospitals and between the control and intervention groups.

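### The named linear and Poisson models have no provision for a rescue time that most patients lack, or for day and event counts more variable than Poisson allows (secondary outcomes only)

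*Protocol article*

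**What the plan says.** The Outcome measures section of the protocol article lists among the secondary outcomes "time to implement rescue therapy, length of stay in hospital, length of stay in a high-care unit". The Research questions section also asks about time to rescue, and about "the utilization of high-care and intensive care facilities after complications, and the length of stay in these units".

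The Statistical analysis section sorts outcomes by type. For the primary and binary secondary outcomes, "multi-level mixed effect logistic regression with random time by cluster interaction will be used". For the rest: "For continuous secondary outcomes, multi-level mixed effect linear regression will be used and for countable secondary outcomes, multi-level mixed effect Poisson regression models". A general sentence follows: "Adjustments will be made for temporal trends and for clusters within hospitals". The same section says that, once a hospital has crossed over, its patients are analysed by intention to treat.

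The article does not say which outcome goes to which model, who enters the time-to-rescue analysis, or how in-hospital deaths enter length of stay. The random time-by-cluster term is written only in the sentence on the logistic model.

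**The concern.** A time to rescue is neither binary nor a count of events, so under the stated rule it goes to the linear model. That model needs a value for every patient it uses, and a patient who was never rescued has none. Whether a patient has a value is settled after allocation, and the intervention influences it, because the visits exist to find complications and prompt treatment. A difference in mean rescue time between phases would then mix speed of rescue with a change in who gets rescued. It could favour either phase. Earlier detection is the trial's proposed mechanism, so a misleading result here would colour the reading of the mortality result.

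The second issue is the error variance of counts. Poisson regression sets the variance equal to the mean, given the model terms. A hospital-level random effect does not absorb extra variation between patients within a hospital. If lengths of stay in days or numbers of events are analysed this way and vary more than Poisson allows, the intervals are too narrow and false-positive findings become more frequent.

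**Working it through.** **The plan's own figure.** The Sample size calculation section states: "In order to detect a reduction from 2% to 1% in postoperative 30-day mortality, with an alpha of 0.05 and a power of 80" per cent, and "a 1:1 ratio between control and intervention group, a total of 4638 patients have to be included". With two-sided alpha 0.05 and pooled variance, n per group = [1.960·√(2·0.015·0.985) + 0.842·√(0.02·0.98 + 0.01·0.99)]² / 0.01² = 2319 after rounding up, so 2 × 2319 = 4638. It reproduces. Then 4638 × 1.2 = 5566, rounded to 5600 (8 × 700). This confirms the total and the mortality rates used below. The article gives no figure for time to rescue or length of stay.

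**1. Who can have a rescue time.** The Background section states: "Perioperative complications occur in approximately 30–40% of non-cardiac surgical patients".
- If every patient with a complication is rescued: 5600 × 0.30 = 1680 and 5600 × 0.40 = 2240. So 60–70% have no rescue time.
- If only 25–50% of them receive rescue therapy (assumed): 5600 × 0.30 × 0.25 = 420 up to 5600 × 0.40 × 0.50 = 1120. So 80–92.5% have none.

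*How the sign can reverse (assumed figures).* Control rescues 100 patients at a mean of 24 h. Intervention rescues the same 100 at 20 h, and also 40 who would have been missed, at 72 h. The intervention mean is (100 × 20 + 40 × 72)/140 = 4880/140 = 34.9 h. Every patient is treated sooner or newly treated, yet the mean is longer.

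**2. Poisson intervals.** Let φ be variance/mean. The Poisson standard error is too small by √φ, so a nominal 95% interval covers P(|Z| < 1.96/√φ).
- φ = 2: P(|Z| < 1.386) = 0.83.
- φ = 5: P(|Z| < 0.877) = 0.62.

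This was checked in a simulated stepped wedge with no true effect: 8 hospitals, 9 equal periods, 78 patients per cell (5616 in all), and negative binomial stays with assumed mean 5 days. The random-effect model was approximated by REML on log cell means, with 1500 runs per row.

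| Assumed SD (days) | φ | Type I error, hospital and period terms only | With hospital-by-period random effect |
|---|---|---|---|
| 3 | 1.8 | 13.6% | 4.3% |
| 5 | 5.0 | 38.1% | 5.4% |
| 8 | 12.8 | 58.2% | 5.3% |

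The extra term works because patient-level overdispersion shows up as extra variance of the cell means, which a cell-level random effect can take up. The simulation used equal cells; with unequal cells the absorption is only approximate.

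**3. Early death and length of stay.** Assume survivors stay 5 days on average and patients who die stay f times as long. Mortality is 2% in control and 1% in intervention.
- f = 0.25: control 0.98·5 + 0.02·1.25 = 4.925; intervention 0.99·5 + 0.01·1.25 = 4.9625; shift +0.0375 day.
- f = 0.5: shift +0.025 day.
- f = 2 or 3: shift −0.05 or −0.10 day, so the sign depends on how long those who die stay.

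For scale, the patient-level standard error of the difference, SD·√(2/2800), is 0.08, 0.13 and 0.21 day for SD 3, 5 and 8. It ignores clustering and time adjustment.

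**The case against.** The strongest reply is that much of this is read into silence. This is a condensed article; the full protocol and any analysis plan are not shown, and analysis sets, time origins and the handling of deaths are normally set there. That stands for those details. It does not stand for the choice of model family, which the article fixes by outcome type; a time-to-event or negative binomial analysis would depart from the published rule.

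Several stronger readings are tempting, and the documents do not support them:
- *The models ignore the design.* They are multilevel, and adjustment for temporal trends and clusters is stated.
- *The plan drops unrescued patients and scores an early death as a good short stay.* Neither is written. The first follows if a linear model is applied to rescue times. The second follows if deaths are left unmarked, and its effect is small.
- *The Poisson intervals are wrong.* That requires days or events to be modelled as counts, overdispersion (no variance is given) and no hospital-by-period random effect. The countable outcomes could be numbers of complications only. Stays sent to the linear model escape this problem, because that model estimates its residual variance.

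Two further objections stand. The 30–40% rate is for non-cardiac surgical patients in general, while this cohort is selected for risk, so the true share could be higher. And cumulative incidence of rescue in all patients answers a different question: preventing complications lowers rescue incidence and could be misread as slower rescue. Replacing the outcome outright is therefore debatable; adding the all-patient analysis is not.

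**Conclusion.** The point holds in a limited form and concerns secondary outcomes only.

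- **Time to rescue.** This is the firmest part. Under the stated rule the comparison rests on at most about 30–40% of 5600 patients at the cited rate, selected after allocation and partly by the intervention. It cannot be read as a comparison of the randomised phases, and it sits badly with the article's own intention-to-treat statement. The direction of bias is unknown; the 34.9 h example shows only that a reversal is possible.
- **Counts.** This part is conditional. At an assumed φ of 2 to 5, coverage falls to about 83–62% without a hospital-by-period random effect. Over the assumed SDs of 3 to 8 days, type I error was about 14–58% without that term and about 4–5% with it. The article states the term for the logistic model and neither states nor excludes it for the Poisson model.
- **Early death in length of stay.** The shift is about 0.025–0.04 day if those who die stay a quarter to a half as long as survivors. It justifies a sensitivity analysis at most.

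**What to change.** 1. **Time to rescue.** Report the comparison among rescued patients as descriptive. Add an analysis of all enrolled patients from the end of surgery: cumulative incidence of first rescue therapy, with death and discharge alive as competing events, adjusted for hospital and calendar time. Present it beside complication incidence, so that prevention is not mistaken for slow rescue.
2. **Counts of days or events.** Replace mixed Poisson with mixed negative binomial regression, and state that the random time-by-cluster term applies to all secondary models, not only the logistic one. If sandwich variance is preferred, eight hospitals are too few without a small-sample correction.
3. **Length of stay.** State which model each stay outcome uses. As an optional sensitivity analysis, use time to discharge alive with death competing, or days alive and out of hospital to day 30.

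The cost is a few lines of analysis wording, a little more analysis work and wider intervals. The design and patient numbers do not change, and R is already named as software. The Trial status section reports recruitment incomplete at submission, so the change could have been specified before results were known.

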**Methods:**

TRACE is a prospective, multicenter, stepped-wedge cluster randomized interventional study in academic and peripheral hospitals in the Netherlands. All hospitals start simultaneously with a control phase in which standard care is provided. Sequentially, in a randomized order, hospitals cross over to the intervention phase in which patients at risk are routinely followed up by an anesthesia professional at postoperative days 1 and 3, aiming to detect and prevent or treat postoperative complications. We aim to include 5600 adult patients who are at high risk of developing complications. The primary outcome variable is 30-day postoperative mortality. Secondary outcomes include incidence of postoperative complications and postoperative quality of life up to one year following surgery.

Statistical analyses will be performed to compare the control and intervention cohorts with multilevel linear and logistic regression models, adjusted for temporal trends and for clusters (hospitals). The time horizon of the economic (cost-effectiveness) evaluation will be 30 days and one year following surgery.

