### Recruitment and consent

Patients will be recruited by a member of study team (anesthesiologist or research assistant) preoperatively, either during the preoperative screening or directly after hospital admission. Patients receive a written patient information letter and are additionally orally informed about the study aims and the study phase they will enter (control or intervention). If they agree to participate, they will be asked to sign informed consent.

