### Data collection

Patient and clinical data will be collected at several time-points during the study period: at inclusion (baseline); intraoperatively; postoperatively at days 1 and 3; during hospital stay; from hospital discharge until 30 days; and until 12 months. Data records will be coded and transcribed by local investigators into an Internet-based electronic case record form.

Data to be collected from patient record files include patient baseline characteristics, data on surgery and anesthesia, intraoperative adverse events, the postoperative clinical course, postoperative in-hospital adverse events, and post-discharge events measured at 30 days and at 12 months after the date of surgery. During the intervention period, data collection additionally includes anesthesia interventions on postoperative days 1 and 3.

Data will also be collected from patient questionnaires, completed at inclusion, seven days, 30 days, and 12 months postoperatively. The questionnaires include questions on quality of life (EuroQol Dutch EQ-5D-5 L), pain scores (numeric rating scale, NRS), functional recovery (Functional Recovery Index), and expected/perceived recovery (Global Surgery Recovery index). See Fig. 2 for an overview of enrolment, intervention, and assessments.

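### The stated adjustment set for the continuous secondary outcomes does not name the EQ-5D-5L value taken at inclusion, which costs precision on quality of life (low severity)

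*Protocol article*

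**What the plan says.** - **Model.** Statistical analysis: "For continuous secondary outcomes, multi-level mixed effect linear regression will be used". No patient-level term is named in that sentence.
- **Adjustments.** The same section continues: "Adjustments will be made for temporal trends and for clusters within hospitals". The Methods paragraph of the abstract ties this to the linear models: "multilevel linear and logistic regression models, adjusted for temporal trends and for clusters (hospitals").
- **Baseline data.** Data collection: "Data will also be collected from patient questionnaires, completed at inclusion, seven days, 30 days, and 12 months postoperatively". On content: "The questionnaires include questions on quality of life (EuroQol Dutch EQ-5D-5 L), pain scores (numeric rating scale, NRS").
- **Outcomes.** Outcome measures lists "quality of recovery 30 days after surgery, and postoperative quality of life up to one year following surgery" among the secondary outcomes. Pain is not on that list.
- **Consent.** Recruitment and consent has patients told, before they sign, "the study phase they will enter (control or intervention").

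**The concern.** The plan collects a pre-operative quality-of-life score, analyses the same score after surgery as a secondary outcome, and twice states what the model adjusts for without naming the pre-operative score. Two things are at stake for the quality-of-life part of the fourth research question.

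1. **Precision.** Variation between patients that the inclusion score explains stays in the residual, so the interval for the intervention effect is wider than the data require.
2. **Comparability.** Control and intervention patients are different people recruited in different weeks, and they know their phase when they decide whether to join. If the type of patient who agrees changes when a hospital crosses over, that change lines up with the treatment indicator. Hospital terms remove stable differences between hospitals and time terms remove shared trends. Neither removes a within-hospital shift that occurs at crossover.

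**Working it through.** **The plan's own figures.** The only sample size calculation is for mortality. For 2% versus 1%, two-sided alpha 0.05 (sidedness is not stated) and 80% power, with pooled variance under the null:

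n per arm = [1.960·√(2·0.015·0.985) + 0.842·√(0.02·0.98 + 0.01·0.99)]² / 0.01² = 2319, total 4638, as stated.

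4638 × 1.2 = 5566, against the stated 5600. None of this depends on quality of life.

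**Design inputs.** From Study schedule and randomization: 8 hospitals, 31 weeks, one transition week each, 700 patients per hospital. The crossovers start after week 8 and are complete by week 24. I infer one crossover every two weeks, with transition weeks 9, 11, ..., 23.
- Control hospital-weeks: 8 + 10 + ... + 22 = 120.
- Intervention hospital-weeks: 22 + 20 + ... + 8 = 120.
- Patients per hospital-week: 700/30 = 23.3, so 120 × 23.3 = 2800 per phase, as the article states.

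**Assumed inputs.** The documents give no standard deviation, ICC, cluster autocorrelation or baseline-to-follow-up correlation (ρ) for quality of life. I work in SD units, with ICC 0.01-0.02, cluster autocorrelation 0.8 and ρ from 0.3 to 0.6.

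**Precision.** The generalized least squares variance of the intervention effect is the treatment element of (Σ XᵀV⁻¹X)⁻¹, summed over hospitals. X holds the time terms and the treatment indicator. V has three parts:
- a hospital component, ICC × 0.8;
- a hospital-week component, ICC × 0.2;
- a patient component, (1 − ICC)(1 − ρ²)/23.3, with ρ = 0 when the baseline value is left out.

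Without the baseline value the SE is about 0.055 SD (ICC 0.01) to 0.057 SD (ICC 0.02). With it:

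| ρ | 1 − ρ² | SE ratio, ICC 0.01-0.02 | SE reduction |
|---|---|---|---|
| 0.3 | 0.91 | 0.96 | about 4% |
| 0.4 | 0.84 | 0.92-0.93 | 7-8% |
| 0.5 | 0.75 | 0.88 | about 12% |
| 0.6 | 0.64 | 0.82 | about 18% |

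A smooth 4-df time trend and a separate effect for each week give the same ratios to two decimals. Widening the ranges to ICC 0.001-0.05 and cluster autocorrelation 0.8-1.0 gives 0.95-0.96 at ρ = 0.3 and 0.87-0.90 at ρ = 0.5. If fewer than 5600 questionnaires are returned, the patient component weighs more and the ratio moves towards √(1 − ρ²), which is 0.95 at ρ = 0.3 and 0.80 at ρ = 0.6.

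**Imbalance.** If a baseline difference of δ SD between phases remains after the time and hospital terms, the unadjusted estimate shifts by about ρ × δ. For δ = 0.1, chosen only for illustration, the shift is 0.03 SD at ρ = 0.3, 0.05 SD at ρ = 0.5 and 0.06 SD at ρ = 0.6. At ρ = 0.5 that is close to one standard error (0.05 against 0.055-0.057).

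**The case against.** The strongest reply is that this is a condensed article. It names a model family and the adjustments peculiar to a stepped wedge. It does not say that the list is complete or that inclusion values will be left out, and the full protocol (version 5) or an analysis plan may contain the baseline term. The wording also does not exclude a longitudinal mixed model in which the inclusion score is one of the repeated measurements. This part stands: a reader might infer that the models adjust for time and cluster *only*, but that word is not in the text. What remains is that the article chose to state its adjustments, did so twice, and in the abstract did so for the linear models explicitly. The point therefore rests on a stated method and not on silence alone.

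Four other strong readings are tempting and are not supported:
- **Pain.** Numeric rating scale scores are collected at inclusion, but pain is not a listed outcome, so the planned models cannot be faulted for it.
- **Recovery at 30 days.** Recovery is measured with separate indices. The article does not show that these have a like-for-like value before surgery.
- **Imbalance wholly uncorrected.** The time and hospital terms already remove the part due to secular trend and hospital mix.
- **A baseline difference carried over in full.** It enters in proportion to ρ, and consent with the phase known creates only the possibility of one.

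**Conclusion.** The point holds as a low-severity improvement to a stated method. As written, the quality-of-life model does not name the inclusion EQ-5D-5L value. Under the assumed correlations of 0.3 to 0.6, ICC 0.01-0.02 and cluster autocorrelation 0.8, naming it would reduce the standard error by about 4% to 18%. The size depends mainly on the correlation, which the documents do not give; at the low end the gain is small. Protection against a crossover-aligned baseline shift is a second benefit, but its size cannot be stated because no imbalance is shown. A reader might infer that the analysis is invalid or its estimate biased, and the documents do not support that. The point concerns a secondary outcome and changes neither the mortality analysis nor the 4638 and 5600 figures.

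**What to change.** State that the EQ-5D-5L value at inclusion enters the quality-of-life model as a covariate beside the time and hospital terms, or that baseline and follow-up scores are modelled jointly in one mixed model. State also that patients with a missing baseline are kept, by simple imputation of the baseline value or through the joint model. Do the same for the pain score only if it is analysed as an outcome. If the full protocol or analysis plan already says this, a confirming sentence is enough.

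The cost is one covariate per model plus a rule for missing baselines, using data already being collected. Fixing it before outcomes are compared by phase also prevents a later choice between adjusted and unadjusted results.
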